### Testing procedure

#### Time-points

In accordance with recommendations for a core outcome set of measurements, the included time-points refer the time since onset of stroke [24]. Thus, time points included in the prospective cohort are 3-, 6-, 12-, and 18-months post-stroke (T3, T6, T12 and T18). Onset of stroke (T0) refers to within 3 days of onset of symptoms [24]. Time points included in the RCT are pre-intervention (Pre) and post-intervention (Post). Subsequently, a follow-up will be conducted 6 months after termination of intervention (Follow-up). Time since stroke will be reported with the study findings for the RCT. The primary time point is immediately after 6 months training (Post) (cf. Table 1).

**Table 1 Tab1:** Study Outcomes and Time-Points

**Prospective cohort**	**T3**	**T6**	**T12**	**T18**
IPAQ	x	x	x	x
EQ-5D	x	x	x	x
Fatigue Severity Scale 7	x	x	x	x
Modified Rankin Scale	x	x	x	x
Blood Biomarkers	x			
**RCT**		**Pre**	**Post**	**Follow-up**

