### Outcome measurements

#### Primary outcome

The primary outcome measurement is the between-group difference in the change score of the Fugl-Meyer Lower Extremity Assessment (FM-LE) from pre- to post-intervention on the intention-to treat population. The FM-LE assesses motor function [27] and has been recommended as a part of a core outcome set in stroke rehabilitation studies [24] and is commonly used in stroke research to evaluate motor recovery due to its clinometric properties [28, 29]. The FM-LE assesses reflex activity, voluntary movement, and coordination and velocity of movement through a 0–34 point ordinal scale with each item scored as: 0 = cannot be performed, 1 = partially performed, and 2 = performed completely [27, 30].

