### Statistical Analysis

#### Primary Analysis

An assessor-blinded intention-to-treat (ITT) analysis will be performed on primary and secondary outcome measures (Primary Analysis). The ITT analysis will employ a two-way analysis of variance (ANOVA) to analyse between-group differences in change-scores from pre- to post-intervention. No interim analysis will be performed. Full analysis data sets will be created with multiple imputation as part of a sensitivity analysis to examine the robustness of the primary analysis.

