#### Sample size calculation

A priori two-sided sample size calculation for two independent groups was performed and resulted in a required sample size of 34 study participants in total. This was based on detecting a minimally clinically important between-group difference (MCID) of 6 points on the FM-LE scale [55] and a standard deviation of 6 points [28, 30, 55] at an α level of 5% and with a statistical power of 80%. Allowing for dropout the aim is to include 40 participants in total.

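### The primary analysis is labelled intention-to-treat, but as specified it can use only participants with a Post FM-LE and does not adjust for baseline; a baseline-adjusted model and a delta-adjusted check are cheap improvements

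*Protocol article*

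**What the plan says.** Under Primary outcome, the endpoint is the between-group difference in FM-LE change "from pre- to post-intervention on the intention-to treat population". Under Primary Analysis, the method is a "two-way analysis of variance (ANOVA) to analyse between-group differences in change-scores from pre- to post-intervention". The same paragraph places imputation elsewhere: "Full analysis data sets will be created with multiple imputation as part of a sensitivity analysis to examine the robustness of the primary analysis". No other handling of missing values is given for the primary analysis.

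Table 1 marks FM-LE at Pre and Post only, and Time-points names Post as the primary time point. Under Sample size calculation, 34 participants are required, and then: "Allowing for dropout the aim is to include 40 participants in total". No dropout rate is stated. A separate per-protocol analysis of adherent participants is listed under Secondary analyses. A separate statistical analysis plan is announced and is not shown.

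**The concern.** Three choices are fixed together: a change-score model, an outcome measured at only two visits, and imputed full data sets confined to the sensitivity analysis. The set actually analysed is then randomised participants who have a Post value, while the label promises the intention-to-treat population.

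The label matters less than what the model does with the loss. A change score is normally related to its own baseline. If those lost differ in baseline severity from those kept, and differ more in one arm than in the other, the unadjusted comparison of completers' change scores shifts. Some loss is foreseeable: the programme lasts six months, the participants are moderately to severely disabled, and the Adverse Events section itself names recurrent stroke, re-hospitalisation and death as risks. The planned check has a limit as well. Standard multiple imputation assumes missingness at random, so it cannot test whether the result survives loss that depends on the unseen outcome.

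**Working it through.** **1. The plan's own figures.** Inputs from Sample size calculation: difference 6, SD 6, two-sided 5%, power 80%; 1:1 allocation from Randomisation. The two-sample t-test (noncentral t) gives 78.1% power at 16 per arm and 80.7% at 17 per arm, so 34 is reproduced. The implied allowance is (40 − 34)/40 = 15%, and 34/0.85 = 40.

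**2. Who enters.** Change = Post − Pre, so a missing Post means a missing change. The second factor of the two-way ANOVA is not named. Whether it is time or a stratum, a participant without a Post value still contributes nothing to the contrast.

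**3. Loss that depends on baseline.** Assumed, not in the protocol: Pre SD 7, Pre–Post correlation r = 0.7, true effect 6, 20 per arm. The slope of Post on Pre is β = r × SD(Post)/SD(Pre). If completers' mean Pre exceeds that of all randomised by d in the robot arm and by e in control, then

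bias of the change-score difference = (β − 1)(d − e).

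- Random 15% loss in control gives e = 0.
- The extreme case in the robot arm loses exactly the lowest 22%: d = 7 × 0.296/0.78 = 2.66, where 0.296 is the normal density at the 22% point.
- With equal SDs at Pre and Post, β = 0.7 and the bias is −0.3 × 2.66 = −0.80, so the estimate averages 5.2.
- With a Post SD of 6.6, β = 0.66 and the bias is −0.34 × 2.66 = −0.90, so 5.1.
- Simulated trials with weaker dependence at the same 22% reach about 5.7.

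The illustrative range is therefore 5.1 to 5.7, a bias of 0.3 to 0.9 points, or 5% to 15% of the target (0.3/6 and 0.9/6).

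**4. Sensitivity to the assumed SD.** The protocol does not say whether its SD of 6 refers to change. If it does, 36 = 49 + s² − 9.8s gives a Post SD s of 8.2 and β = 0.82. The extreme case then costs 0.18 × 2.66, about 0.5 points, and the estimate averages about 5.5.

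**5. Equal selection.** If d = e, the bias is zero. Simulations with the same baseline-dependent loss in both arms averaged 5.97 to 6.04.

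**6. What removes the bias.** In the scenarios of step 3, regressing Post on arm and Pre, in the same completers with nobody imputed, averaged about 6.04. The correction comes from using baseline, not from imputation as such.

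**7. Loss that depends on the unseen outcome.** If those lost would have changed g points less than completers in their arm, bias = g × (share missing in robot arm − share missing in control), here overstating the effect. For g = 3 to 6:

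| Missing, robot vs control | Bias (points) |
|---|---|
| 15% vs 15% | 0 |
| 20% vs 10% | 0.3 to 0.6 |
| 30% vs 0% (all six in one arm) | 0.9 to 1.8 |

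Neither baseline adjustment nor missing-at-random imputation addresses this.

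**8. Scale.** With 17 per arm and SD 6, the standard error of the difference is 6 × √(2/17) = 2.06. With no loss of information, 20 per arm would give 86.9% power.

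**The case against.** The strongest reply is that observed cases as primary with imputation as sensitivity is a recognised arrangement, that the article announces a separate analysis plan, and that the words complete case appear nowhere. A reader might infer that the analysis definitely discards up to 15% of those randomised. The documents do not support that: no dropout rate is stated, 15% is only the allowance implied by 34 and 40, and actual loss could be lower or higher. Stopping training also need not mean a missed Post test. Because the per-protocol analysis is separate, non-adherent participants who are tested stay in the primary analysis, so that part of intention-to-treat is kept.

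It is also fair that bias requires selection to differ between arms, for which the protocol gives no evidence, and that the illustrative biases are below one standard error. A reader might further take the figures as proof that imputation must be primary. Step 6 shows otherwise: with only Pre and Post measured, imputing from Pre adds little over adjusting completers for Pre.

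What does not stand is full deferral to the analysis plan. The article has already chosen the primary model and assigned imputation to sensitivity; a later plan that reversed this would change the protocol, not complete it.

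**Conclusion.** The point holds as a cheap improvement, not as a flaw that undermines the trial. As written, the headline result rests on randomised participants with a Post FM-LE, under an unqualified intention-to-treat label and without adjustment for baseline. With baseline-dependent loss confined to the robot arm, the average estimate falls to about 5.1 to 5.7 for a true 6. That rests on an assumed Pre SD of 7, r = 0.7 and 22% versus 15% loss; the shift is smaller if the protocol's SD of 6 describes change, and nil if selection is equal in both arms. Outcome-dependent loss can push the other way, and the planned imputation would not reveal it. A reader might infer that the trial is underpowered through these exclusions; it is not, since 34 analysed is what the calculation requires.

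**What to change.** 1. Make the primary model Post FM-LE on arm with Pre FM-LE and the mRS randomisation stratum as covariates, using every randomised participant with data in the assigned arm, whatever their adherence.
2. Describe the primary set accurately: randomised participants with a Post value, assuming missingness at random given baseline. Alternatively, include all randomised participants by imputation. Either is defensible; the unqualified label on the current specification is not.
3. Keep the standard multiple imputation and add a delta-adjusted version, in which imputed Post values are shifted by a range of penalties varied separately by arm, reporting where the conclusion would change.

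The cost is a little more analysis work and a less favourable description of the primary population. No extra participants or visits are needed. If imputation is made primary, power should stay close to 80.7% at 15% loss unless useful auxiliary variables are available.

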#### Secondary analyses

Secondary analyses will employ ANOVA to analyse between-group differences in change-scores in the per-protocol dataset (only including participants demonstrating acceptable adherence of > 70%). Secondary analyses will also be performed to evaluate long-term outcome (follow-up 6 months after post-intervention testing) and to evaluate tertiary outcomes not included in the main RCT manuscript.

#### Statistical analysis plan

A separate statistical analysis plan, including potential deviations from trial protocol and their related consequences, will be made publicly available on ClinicalTrials.gov prior to analysis. Unblinding will be performed following the completion of the primary analysis.

#### Sample size calculation

A priori two-sided sample size calculation for two independent groups was performed and resulted in a required sample size of 34 study participants in total. This was based on detecting a minimally clinically important between-group difference (MCID) of 6 points on the FM-LE scale [55] and a standard deviation of 6 points [28, 30, 55] at an α level of 5% and with a statistical power of 80%. Allowing for dropout the aim is to include 40 participants in total.

### Dissemination

Positive, negative, or inconclusive findings will be summed up in manuscripts and submitted at international peer-reviewed scientific journals, presented at international conferences, and published in a PhD dissertation.

## Discussion

This trial is designed to investigate if an intervention based on robot-assisted dynamic BWU yields superior effects on motor function, physical function, fatigue, and quality of life in a chronic stroke population with moderate to severe impairments. This type of intervention may be particularly relevant for this subpopulation within stroke, as BWU-based training may facilitate a more appropriate intensity, volume, and task-specificity thereby leading to superior functional recovery. Non-ambulatory stroke-affected individuals are underrepresented in the scientific literature [4, 9] and thus the trial will not only determine the efficacy of BWU-based interventions for this subpopulation but also contribute to the knowledge on rehabilitation of moderately-to-severely impaired stroke-affected individuals. If the current trial, based upon a controlled and standardized intervention with a high degree of internal validity demonstrates a clear efficacy, the effectiveness of this BWU-training method in a more pragmatic and practice-oriented setting should be investigated. This would be highly relevant to investigate at municipal level rehabilitation, as not all clinics own the costly assistive devices found at higher levels of specialisation in neurorehabilitation. In contrast to such devices, the presently implemented robot is designed with a low-cost principle for ease of broad scale implementation. Taken together, the present trial contributes to the scientific literature on the efficacy of BWU, the rehabilitation of moderately-to-severely impaired stroke-affected individuals, and the findings may guide future studies investigating the effectiveness of BWU in clinical settings.

## Data Availability

The datasets used and/or analysed during the current study are available from the corresponding author upon reasonable request.
